#### Primary outcome—Cognition

Cognitive functioning will be assessed via videoconference, using validated remote versions of paper-pencil neuropsychological assessments [37] and computerized tasks, both performed under the supervision of a research team member. G*eneral cognitive functioning* will be tested using a remote version of the Montreal Cognitive Assessment (MoCA) [38]. The remote version of the MoCA is identical to the original version, to the exception that one question in the orientation subscale is modified (“Now, tell me the name of this place, and which city it is in” was replaced by one question regarding an important sightseeing place in Canada). In addition, the *three main components of cognition* will be assessed with a comprehensive neuropsychological assessment, including both paper-pencil tests and computerized tasks, from which composite z scores will be calculated: executive functions, processing speed, and episodic memory. These different composite *Z*-scores will first be computed by grouping tests and subscores that conceptually assess the same cognitive functions (mean of *z*-scores of different tests and scores). In a second step, internal consistency among each composite *z*-score will be verified with Cronbach’s alphas as done previously (*α* > .7) [39]. The neuropsychological assessment will include the following paper-pencil tests that will be administered in a fixed order: Rey auditory verbal learning test [40], Digit Span, an oral Trail Making Test with three conditions (1—counting from 1 to 20 (maximum of 30s); 2—naming letters from A to Z (maximum of 30 s); 3—alternating between naming numbers and letters in chronological and alphabetical order (e.g., 1-A-2-B) (maximum of 30 s) [41]), Phonological and Semantic Fluency from the D-KEFS battery (Letters P, T, L (60 s maximum); Categories: animals, men’s names (60 s maximum); Switching between naming fruit and furniture (60 s maximum) [42]), and Similarities subtest from the WAIS-IV [43]. These tests are validated and normalized for an older adult population [40, 44, 45]. The Similarities subtest will only be administered at baseline to obtain a measure of crystallized intelligence; it will be optional and performed according to the level of the participant’s fatigue. Participants will also complete a computerized assessment on their tablet or computer [32]. The computerized tasks include a dual-task [32], Stroop task [33], and N-back [34], all in trained and transfer versions (same tasks but with different stimuli) presented in a counterbalanced order between the participants via a Latin square procedure. Subcomponents of each task allow the dissociation of attentional control mechanisms from mere cognitive speed. Importantly, the tasks record response time in milliseconds reducing the likelihood of ceiling effects. These tasks also tend to be more sensitive to training effects. The trained and transfer task comparison allows quantifying participants' ability to transfer cognitive training effects to another task. The computer equipment (i.e., computer or tablet) used by the participant for the computerized tasks will be systematically documented. Participants will be requested to use the same computer equipment for the four testing sessions.

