## Methods/design

### Design

COVEPIC is a randomized, single-blind trial with two parallel intervention arms:
*Arm 1 – Physical exercise*: remote monitoring and counseling of home-based physical exercise.*Arm 2 – Physical exercise and cognitive training*: remote monitoring and counseling of home-based physical exercise and home-based cognitive training.

The study design includes six months of intervention. All participants will be assessed at baseline, 3 months, and 6 months. At each timepoint, four testing sessions will be done remotely using videoconference supervision and online questionnaires over a period of 7–10 days. At twelve months (6 months after the end of the intervention), a follow-up assessment will be performed to explore the potential maintenance of intervention effects. Participation in this follow-up assessment will be left to the participant's discretion, as it does not directly address the main hypotheses. The trial was designed according to SPIRIT guidelines (cf. SPIRIT checklist in the additional file) [28]. Figure 1 illustrates the trial design according to items of SPIRIT figure, which is also available in additional files.

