
**Table 1 Tab1:** List of assessments across the study timepoints according to the remote method used

Remote method	Domain	Procedure	T-1	T0	T1	T2	T3
**Phone call**	**-**	Written informed consent	X				
		Mini-Mental State Examination	X				
		Physical activity readiness questionnaire	X				
		Technology tutorial	X				
**Online videoconference**	**Cognition**	Montreal Cognitive Assessment		X	X	X	X
		Oral Trail Making Test		X	X	X	X
		Verbal Fluency Test		X	X	X	X
		Digit Span test		X	X	X	X
		Similarity Test		X	X	X	X
		Rey auditory verbal learning test		X	X	X	X
		Computerized trained cognitive task		X	X	X	X
		Computerized transfer cognitive task		X	X	X	X
	**Physical functions**	One leg balance test		X	X	X	X
		5-time Sit-to-stand test		X	X	X	X
		Timed Up and Go test		X	X	X	X
		4-meter walking speed test		X	X	X	X
**Online self-reported forms**		Matthews Questionnaire		X	X	X	X
	**Quality of life**	12-Item Short Form Survey		X	X	X	X
	**Mood and anxiety**	State Anxiety Inventory		X	X	X	X
		Geriatric Depression Scale		X	X	X	X
		Perceived Stress Scale		X	X	X	X
		Perseverative Thinking Questionnaire		X	X	X	X
		Connor-Davidson Resilience Scale 10		X	X	X	X
		Intolerance of Uncertainty Scale		X			
		Trait Anxiety Inventory		X			
		Anxiety sensitivity Index		X			
	**Social environment**	Social and Community Involvement Questionnaire		X	X	X	X
		Lubben Social Network Scale		X	X	X	X
	**Sleep**	Pittsburgh Sleep Quality Index		X	X	X	X
		Berlin Questionnaire		X	X	X	X
	**Nutrition**	Short Diet Questionnaire		X			X
	**Prior Physical activity**	Physical Activity Scale for the Elderly		X			
	**Cognitive reserve**	Cognitive reserve Questionnaire		X			
	**Gender**	Bem Sex-Role Inventory		X			
	**Medical history**	Medical Questionnaire		X			
	**COVID-19 repercussions**	QCOVID Questionnaire		X			

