#### Physical exercise and cognitive training

The combined multidomain intervention will include home-based physical exercise and cognitive training. Home-based physical exercise will be exactly similar to the conditions described in the previous section. Due to the important variations observed in the short-term effect of exercise on cognitive performances [31], home-based cognitive training will either take place prior to the exercise session or at least 3 h post-exercise training. Participants will be asked to complete their cognitive training in a quiet and comfortable setting without distraction. Both validated computerized cognitive tasks and video capsules will be provided to the participants. Participants will be encouraged to perform at least three sessions per week (30 min/session): two sessions of computerized cognitive tasks and the other one dedicated to the video capsules.

For the computerized cognitive training sessions, the following three tasks will be available: (1) dual-task training that requires participants to maintain and prepare for many response alternatives and to share attention between two concurrent tasks (i.e., Dual-task [32]), (2) inhibition training, which requires the participants to refrain from giving an automatic response (i.e., Stroop task [33]), and (3) working memory training, which asks participants to maintain and update information in working memory to recall items presented earlier (i.e., N-Back task [34]). Each cognitive task lasts approximately 15 min possesses its respective sets of visual stimuli (e.g., letters, numbers, symbols) and matching button symbols. Participants will be instructed to perform the tasks as fast as possible while maintaining accuracy. The three tasks will be presented in a fixed order for all the participants. The level of difficulty of each cognitive task will be gradually increased over the course of the participant’s cognitive training to avoid cognitive task automatization and to maintain stimulation [35]. These computerized tasks will also include visual feedback as well as a histogram of daily performances to encourage improvement and maintain motivation.

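### No rule keeps the trained computerised tasks out of the primary composites, so an arm-by-time effect on executive functions or processing speed could partly or wholly be task practice

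*Protocol article*

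**What the plan says.** Primary outcome—Cognition names MoCA and three composites: executive functions, processing speed and episodic memory. The composites come from an assessment "including both paper-pencil tests and computerized tasks, from which composite z scores will be calculated". Each composite is a plain average of z-scores "of different tests and scores", grouped by the function they are thought to measure. The computerised tasks are a dual-task, a Stroop task and an N-back, "all in trained and transfer versions (same tasks but with different stimuli"). Table 1 lists "Computerized trained cognitive task" under Cognition at T0 to T3, on a separate row from the transfer task. The same section says of the computerised tasks: "These tasks also tend to be more sensitive to training effects". It adds that comparing trained with transfer versions will quantify transfer.

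Physical exercise and cognitive training introduces the practice material with "For the computerized cognitive training sessions, the following three tasks will be available", then lists dual-task, Stroop and N-back. The weekly target is three 30-minute sessions: "two sessions of computerized cognitive tasks and the other one dedicated to the video capsules". Arm 1 receives only "remote monitoring and counseling of home-based physical exercise" (Design).

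Planned data analysis takes a significant intervention-by-time interaction in the primary outcome as evidence of a differential effect of the two interventions. It takes a significant pre-to-post change as evidence of efficacy.

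**The concern.** The arms differ in how much they rehearse material that, as the outcome is defined, feeds the outcome. The exercise arm meets the trained versions only at the assessments. The combined arm also works on the same three tasks for 6 months. People get better at a task they rehearse, and such a gain need not extend beyond that task.

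If trained-version scores are averaged into a composite, a gain confined to them moves the composite. The analysis section would then count the resulting interaction as added benefit for cognition. The arm comparison is labelled the secondary hypothesis, but it is the trial's only randomised contrast and the one used for the sample size. The pooled pre-to-post test, labelled primary, is exposed as well, because about half of its participants are in the combined arm. Blinding of assessors does not address this.

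**Working it through.** **The plan's own figures (Sample size calculation).** Planned difference: 0.425 − 0.239 = 0.186. Standardised: 0.186 / 0.298 = 0.624, as stated. The stated 49 per group does not reproduce. A two-group t test with these inputs reaches 80% power at 42 per group, and 49 gives 86.4%. That mismatch is conservative, is a separate matter, and does not bear on this point.

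**Overlap between training and outcome.**
- Practised in the combined arm: dual-task, Stroop, N-back.
- Assessed for the composites: dual-task, Stroop, N-back, in trained and transfer versions.
- Rule on which version enters a composite: none stated.

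**Training target.** Two computerised sessions × 26 weeks × 30 min = 26 h if the target is just met, or 26 / 3 ≈ 8.7 h per task if shared equally. Actual exposure is unknown, because the Interventions section lets participants set their own dose.

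**Size of the shift.** Let w be the share of a composite's scores that are trained versions. Let g be the extra gain, in z units, of the combined arm over the exercise arm on those scores, with no arm difference on any other score. Since the composite is an unweighted mean,

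shift in the arm difference = w × g.

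Neither w nor g is in the document, so the values below are assumptions. The last two columns use the planned 0.186 and SD 0.298, and assume that both are on the composite's scale. The chance of p < 0.05 is from the noncentral t with 49 per group, two-sided.

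| w | g | shift w × g | chance of p < 0.05 | g needed for 0.186 (= 0.186 / w) |
|---|---|---|---|---|
| 1/8 | 0.5 | 0.0625 | 18% | 1.49 |
| 1/8 | 1.0 | 0.125 | 54% | 1.49 |
| 1/4 | 0.5 | 0.125 | 54% | 0.74 |
| 1/4 | 1.0 | 0.25 | 98% | 0.74 |
| 1/3 | 0.5 | 0.167 | 78% | 0.56 |
| 1/3 | 1.0 | 0.333 | >99% | 0.56 |

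**Pooled pre-to-post test.** With 1:1 allocation, a shift in one arm adds half its size to the pooled change. At w = 1/4 and g = 0.5 that is 0.125 / 2 = 0.0625. A shift equal to the planned difference would add 0.186 / 2 = 0.093.

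**With trained versions excluded.** w = 0, so the direct shift is 0. Any practice effect that carries over to the transfer versions would remain.

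**The case against.** The strongest reply is that the article does not list which scores enter which composite, and that such lists usually sit in a full protocol or analysis plan that is not shown. The article also gives the two versions a purpose of their own, the trained-versus-transfer comparison, and Table 1 keeps them on separate rows. Both fit a plan that analyses them apart. This lowers the certainty that trained scores will be used. It does not settle the matter: the stated definition draws the composites from the computerised tasks, describes those tasks in both versions, and sets none aside. A planned comparison of versions is not a rule for what the composite contains.

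Some stronger readings are tempting but not supported:
- A reader might infer that the whole primary outcome is affected. On the tests listed, MoCA and episodic memory contain no trained computer task.
- A reader might infer that practice would produce the entire planned difference. That holds only for some assumed pairs of w and g. At w = 1/8 and g = 0.5 the shift is about a third of 0.186 (0.0625 / 0.186 = 0.34).
- A reader might call the randomised comparison biased. A gain on trained tasks is a real effect of the assigned intervention. What is at risk is its interpretation as a gain in cognition. Because MoCA, the paper-pencil tests and the transfer versions are collected in both arms, the two can be told apart if they are analysed apart.
- A reader might take the Cronbach's alpha step as reshaping the composites. The text only has it verify consistency, and the timepoint used is plan detail.

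It also stands that training is encouraged rather than fixed, and that task difficulty is raised over time to limit automatisation.

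**Conclusion.** The point holds for the composites that take computerised scores, most plausibly executive functions and processing speed. As written, task-specific practice in the combined arm can enter these composites, and an interaction on them could reflect that practice in part or in full. The pooled pre-to-post test shares the exposure at half the size.

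The magnitude is illustrative: 0.06 to 0.25 for w from 1/8 to 1/4 and g from 0.5 to 1.0, against 0.186. It rests on assumed w and g, no arm difference on the other scores, and a planned difference and SD that apply to the composite's scale, which the sample size section does not state. The flaw in the outcome definition does not depend on these values.

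**What to change.** Before unblinding:
1. State that the primary composites exclude the trained versions and use the paper-pencil tests plus at most the transfer versions of the computerised tasks.
2. Report the trained versions separately, as a check that training worked and for the trained-versus-transfer comparison already planned.
3. Add a sensitivity analysis with composites from paper-pencil tests alone. Transfer versions are the same tasks with new stimuli, so they remove the practice effect only in part.

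No new data are needed, since Table 1 already schedules both versions at every assessment. The costs are fewer scores per composite, hence slightly lower reliability, and a protocol amendment with ethics board approval as described under Ethical considerations.

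### The trained-versus-transfer comparison can show carry-over to new stimuli within practised tasks, but not transfer to another task as the protocol states

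*Protocol article*

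**What the plan says.** In the Protocol article, section Primary outcome—Cognition, the computerised part of the battery consists of a dual-task, a Stroop task and an N-back, "all in trained and transfer versions (same tasks but with different stimuli". A few sentences later the same section gives the purpose of having two versions: "The trained and transfer task comparison allows quantifying participants' ability to transfer cognitive training effects to another task".

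The section Physical exercise and cognitive training describes what the combined arm practises: "For the computerized cognitive training sessions, the following three tasks will be available", namely a dual-task, an inhibition task (Stroop) and a working-memory task (N-back). Each of these "possesses its respective sets of visual stimuli (e.g., letters, numbers, symbols) and matching button symbols".

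Table 1 gives the second versions their own line, "Computerized transfer cognitive task", from baseline to 12 months. Neither the table nor the text names a different paradigm for that line.

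**The concern.** The two statements in Primary outcome—Cognition do not fit together. If the transfer versions are the same tasks with other stimuli, the comparison contains no other task to transfer to. A participant who has learned how to coordinate two responses, suppress an automatic answer or update a running list may do better on the second version without any gain on a different task.

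What is at stake is how a positive result would be described. One aim of the trial is to establish what cognitive training adds to exercise. A gain on the transfer versions, reported in the protocol's own terms, would read as evidence that training reaches beyond the practised tasks. By the protocol's definition it would be evidence only that training reaches beyond the practised stimuli.

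**Working it through.** The article gives no figure to reproduce here. The check is a comparison of the text.

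**Step 1. Overlap of paradigms.**

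| Paradigm | Trained in the combined arm | Assessed as trained version | Assessed as transfer version |
|---|---|---|---|
| Dual-task | yes | yes | yes, new stimuli |
| Stroop | yes | yes | yes, new stimuli |
| N-back | yes | yes | yes, new stimuli |

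The overlap is 3 of 3. No untrained paradigm enters the comparison.

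**Step 2. What the comparison can separate.** Consider three states of the world for the combined arm.

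| State | Gain on trained version | Gain on transfer version | Gain on different, untrained tests |
|---|---|---|---|
| A. Learning tied to the stimuli | yes | no | no |
| B. Learning general to the task, but not beyond it | yes | yes | no |
| C. Learning that also reaches different tasks | yes | yes | yes |

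Trained against transfer version tells A from B and C. It gives the same pattern under B and C. The statement about another task requires telling B from C, and only the last column does that.

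**Step 3. Exposure.** The target is two computerised sessions a week of 30 minutes. Taking 6 months as about 26 weeks, that is 2 × 26 = 52 sessions, or 52 × 0.5 h = 26 hours on these three paradigms. The exercise-only arm has none outside the assessments. This is a target, since participants may set their own dose (section Interventions). It shows that state B is plausible, but it does not measure its size.

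**Step 4. Scheduled tests that could tell B from C.** Candidates are the paper-pencil tests and the MoCA.

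- Digit Span, oral Trail Making and verbal fluency are marked in Table 1 at baseline, 3, 6 and 12 months, and none is among the three computerised training tasks.
- The Rey verbal learning test is repeated too, but the combined arm is taught mnemonic techniques in a weekly video session, so this test lies close to trained content.
- Similarities is described in the text as baseline only and optional, although Table 1 marks it at every assessment. On the text's account it provides no change score.
- The MoCA is repeated and contains none of the computerised tasks, but it is a general screening score and already a primary measure in its own right.

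The first three are therefore the suitable members of a composite.

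**The case against.** The strongest reply is that nothing planned depends on the phrase. The sections Hypotheses, Sample size calculation, Planned data analysis and Dose-Response exploration do not mention transfer. The added value of cognitive training is judged by the intervention × time interaction on the primary outcome. The MoCA goes through that analysis, and so do composites built from paper-pencil tests as well as computerised tasks. The article also says openly what the transfer versions are, and generalisation to new stimuli is itself a recognised form of transfer. All of this stands, and it limits the point to interpretation.

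A reader might go further and infer that the comparison is uninformative, or that the trial's main conclusion on cognitive training is compromised. The article supports neither. The comparison does separate stimulus-bound learning from task-general learning, and the main conclusion is reached by another route.

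A reader might also infer that the transfer versions share every response rule and screen element with the trained ones, or put a figure on the inflation of a transfer effect. The article does not describe the response mapping of the transfer versions, and the button symbols may change with the stimuli. It gives no data on how much of a trained gain is stimulus-specific, so any figure would be invented.

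What the reply does not remove is the contradiction. An analysis plan or fuller protocol could add detail, but it could not turn the same task into another one. The article never qualifies the claim as near transfer.

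**Conclusion.** The point holds as a misstatement of what one planned comparison can show. By the protocol's own definition, the trained-versus-transfer comparison can demonstrate generalisation to untrained stimuli within three practised paradigms, and no more. The overlap with the training is complete (3 of 3), so no part of the comparison can support the wider claim.

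The consequence is limited to an over-interpreted transfer result. The error rates, the sample size and the test of either hypothesis are unaffected. The conclusion assumes only that the article's definition of the transfer versions is accurate and that no further transfer paradigm lies behind the Table 1 line. It is worth correcting before results are written, because the correction is cheap and changes what may be concluded about transfer.

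**What to change.** 1. In Primary outcome—Cognition, change the stated purpose of the comparison to transfer to untrained stimuli within the same task (near transfer), and use that term wherever the result is reported.

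2. Base any statement about transfer to a different task on a separate supportive analysis: the arm × time contrast from baseline to 6 months on a composite of Digit Span, oral Trail Making and verbal fluency. Name these three members in advance. Include no computerised scores, and leave out the Rey verbal learning test and Similarities for the reasons given in step 4 of the working.

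3. Attribute any difference on that composite to the cognitive training programme as a whole. The combined arm also receives strategy capsules and capsules on sleep, anxiety and nutrition, so the contrast cannot isolate the computerised tasks.

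The cost is one sentence of rewording and one extra supportive analysis on tests already scheduled, with no new visits or burden for participants. The downside for the investigators is that a claim of transfer to a different task becomes harder to reach.
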